## Abstract

**Background:** Uncommonly high rates of pneumonia in patients with acute myocardial infarction (AMI) undergoing primary percutaneous coronary intervention (PCI) have been observed during recent years. Inspiratory muscle training (IMT) could reduce pneumonia in patients undergoing coronary artery bypass grafting and other cardiac surgeries. The relationship between IMT and AMI is unknown. Here, we describe the feasibility and potential benefit of IMT in patients at high risk for pneumonia with AMI who have undergone primary PCI.

**Methods:** Our study is a prospective, randomized, controlled, single-center clinical trial. A total of 60 participants will be randomized into an IMT group and control group with 30 participants in each group. Participants in the IMT group will undergo training for 15 min *per session*, twice a day, from 12 to 24 h after primary PCI, until 30 days post-randomization; usual care will be provided for the control group. The primary endpoint is the change in inspiratory muscle strength, the secondary endpoint included feasibility, pneumonia, major adverse cardiovascular events, length of stay, pulmonary function tests measure, and quality of life.

**Discussion:** Our study is designed to evaluate the feasibility of IMT and its effectiveness in improving inspiratory muscle strength in participants with AMI who have undergone primary PCI.

**Clinical Trial Registration:**
www.ClinicalTrials.gov, identifier: NCT04491760.

## Introduction

Uncommonly high rates (2–7%) of pneumonia have been reported in patients with acute myocardial infarction (AMI), thus increasing the mortality of such patients (1–4). However, other than antibiotic therapy, there are only a few treatment options against infection risk. Therefore, there is an urgent need for developing novel preventive strategies to decrease the risk of pneumonia in these patients. Maximal inspiratory pressure (MIP) is a simple, non-invasive way to evaluate respiratory muscle strength, and it is widely used clinically (5). Inspiratory muscle training (IMT) could significantly increase MIP and has been considered a feasible method to reduce pneumonia in patients undergoing cardiac surgery including coronary artery bypass grafting (6, 7). However, the effect of IMT on patients with AMI is poorly understood. Matos-Garcia and colleagues showed that respiratory muscle strength was impaired in patients with AMI compared to healthy subjects (8), and that such impairment might also later lead to pneumonia. To the best of our knowledge, no research has been performed to evaluate the value of IMT on patients with AMI. Therefore, we aim to conduct 30 days of IMT in patients with AMI who are at high risk of pneumonia and have undergone primary percutaneous coronary intervention (PCI), to evaluate the effectiveness and feasibility of IMT in this population.

## Materials and Methods

### Study Design

This proposed protocol involves a single-center, prospective, randomized study. The study is expected for enrollment from December 1st 2020 to April 30th 2021. All of the participants would be followed up until 30 days post-randomization. Our study protocol and patient information documents have been approved by the ethics committee of Guangdong Provincial People's Hospital [No. GDREC2019521H(R1)] and was registered in clinical trials (www.clinicaltrials.gov, NCT04491760). This study will be performed in compliance with the Code of Ethics of the 1964 Declaration of Helsinki and its later amendments. The study would comply with the Consolidated Standards of Reporting Trials Statements (CONSORT) (9), and provided CONSORT checklist when reported the study results.

### Study Oversight

A specific data safety committee has been guaranteed for the current research, consisting of two cardiologists and one statistician. The cardiologists will be responsible for the review of the in-hospital course and follow-up adverse events of the participants. Then, a safety analysis will be conducted by the statistician at the time the 20th participant is randomized, and the data will be divided into IMT-associated events or non-IMT-associated events.

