### Randomization

A specific computer-generated, randomized number will be placed in a sealed envelope. Researchers will be blinded to the information in envelopes and will select consecutive envelopes to distribute to consecutive participants, thus randomly assigning them to either the IMT group (*n* = 30) or the control group (*n* = 30). See study flow Figure 1.

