### Assessment and Reporting of Adverse Events

Adverse events including all-cause death, recurrence of myocardial infarction, stroke, stent thrombosis, angina, dyspnea, acute heart failure, arrhythmia, and other unforeseeable incidents will be recorded in detail during both the in-hospital and follow-up periods. The reporting and documentation of adverse events will be classified as IMT-related or non-IMT-related. This safety analysis will be conducted at the end of our research among patients who had at least 1 day of outpatient safety data.

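### As described, the safety analyses split adverse events only by attribution to IMT, not by randomised arm, so an excess in the IMT arm of events that also follow AMI would not be visible

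*Protocol article*

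**What the plan says.** Study Oversight sets up a committee of two cardiologists and one statistician. The cardiologists review the in-hospital course and follow-up adverse events. The statistician then carries out a safety analysis "at the time the 20th participant is randomized, and the data will be divided into IMT-associated events or non-IMT-associated events". No other split is named.

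Assessment and Reporting of Adverse Events lists death, recurrent infarction, stroke, stent thrombosis, angina, dyspnea, acute heart failure, arrhythmia and other incidents, recorded in hospital and during follow-up. It states: "The reporting and documentation of adverse events will be classified as IMT-related or non-IMT-related". It continues: "This safety analysis will be conducted at the end of our research among patients who had at least 1 day of outpatient safety data".

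The control arm receives standard care (section headed Invention: IMT). Data Analysis compares pneumonia and MACE between arms by odds ratio and leaves other endpoints to be compared as appropriate. The article describes no tabulation of adverse events by arm, either at the interim look or at the end.

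**The concern.** Relatedness to IMT is a judgement about a single event. A control participant does no training, so a control event can only be labelled unrelated. Several listed events also arise after an infarction without any training; the Discussion itself calls heart failure common in AMI. It also says it is unknown whether the pressure effects of forced breathing lead to clinical adverse events. Whoever assigns the label has little evidence to go on, and can hardly do so without knowing whether the participant trained.

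Randomisation removes the need for that judgement, because the frequency in one arm can be set against the other. If IMT raised the rate of arrhythmia or heart failure and each case was put down to the infarct, the described table would show no signal. The article presents this as the first assessment of the safety of IMT in this population, so its safety statement should use the randomised contrast.

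The outpatient-day condition adds to the problem. A participant who dies before discharge has no outpatient day and leaves the analysis population.

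**Working it through.** The plan attaches no figure to the safety look, so there is none to reproduce. The check has three parts.

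**1. What the described split can show.** Let *a* be IMT-arm events judged related, *b* IMT-arm events judged unrelated, and *c* control events (all unrelated by construction).

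- The table as described gives *a* and *b* + *c*.
- The comparison by arm needs *a* + *b* against *c*.
- Two totals cannot fix three unknowns. If the unrelated total is S, then *c* may be anything from 0 to S.

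Illustration with assumed counts, 10 participants per arm and one event each: *a* = 0, *b* = 4, *c* = 1.

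| Display | First column | Second column |
|---|---|---|
| As described | related: 0 | unrelated: 5 |
| By arm | IMT: 4 of 10 | control: 1 of 10 |

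The first row would be identical for 5 v 0, 4 v 1, 3 v 2, 2 v 3, 1 v 4 and 0 v 5.

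**2. What a table by arm could show at the interim look.** Allocation is "randomly assigning them to either the IMT group (*n* = 30) or the control group (*n* = 30"), so about 10 per arm at 20 participants. Two-sided Fisher tests with 5 events in 20, out of C(20,5) = 15,504 arrangements:

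- 5 v 0: 2 × 252 / 15,504 = 0.033.
- 4 v 1: 2 × (2,100 + 252) / 15,504 = 0.30.

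With no control events, at least 5 IMT events are needed for p < 0.05; 4 v 0 gives 2 × 210 / 4,845 = 0.087. Exact power at 10 v 10 under assumed event rates (control v IMT) is about 6% for 10% v 30%, 30% for 10% v 50%, and 67% for 10% v 70%. The documents give no event rates for these outcomes.

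**3. Follow-up at the trigger.** Study Design says "The study is expected for enrollment from December 1st 2020 to April 30th 2021" and "All of the participants would be followed up until 30 days post-randomization". Uniform accrual is my assumption.

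- Window: 31 + 31 + 28 + 31 + 30 = 151 days; 151 / 60 = 2.52 days per participant.
- 20th randomisation: 20 × 2.52 = about day 50.
- Follow-up of participant *i* at that point: (20 − *i*) × 2.52 days.
- At least 30 days: 20 − *i* ≥ 12, so participants 1 to 8, that is 8 of 20.
- At least 7 days: 20 − *i* ≥ 3, so 17 of 20.
- Observed patient-days, capped at 30: 8 × 30 + 2.517 × (0 + 1 + … + 11) = 240 + 166.1 = 406 of 600, or 68%; the mean is 20.3 days.
- The 20th participant reaches day 30 at about day 80, when 80.3 / 2.517 gives 31 randomised, 11 more than at the trigger.

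Slower early accrual would raise these follow-up figures, and faster early accrual would lower them.

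**The case against.** A journal article condenses the full plan, and table layouts often sit in a committee charter. Nothing in the text forbids an additional table by arm. A reader might infer that the committee cannot see an excess in the IMT arm at all. The documents do not support that: the limit applies to the analysis as described. The criticism still stands, because it concerns a split that the article states in two sections and not a detail left out.

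A reader might also infer that the statistician's look is the only safety check. It is not. The cardiologists review events, participants are telephoned weekly after discharge, and vital signs and adverse events are recorded during in-hospital training. This surveillance is real, but none of it is described as comparing the arms, and recording during training has no control counterpart.

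Nor is the end of the trial without any comparison by arm. Death, recurrent infarction and stroke enter MACE, which Data Analysis compares between arms whatever the attribution, as it does pneumonia. This narrows the gap at the end of the trial to the non-MACE events; the comparison is not tied to the interim look.

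Finally, the gain is modest: at 10 v 10 even 4 v 1 is far from significant. That is correct, and it is why the table is proposed as a display and not as a test.

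**Conclusion.** The point holds for the analyses as described. Splitting only by attribution hides the randomised contrast at the interim look for all adverse events. At the end it does so for those outside MACE and pneumonia: arrhythmia, acute heart failure, angina, dyspnea and stent thrombosis. This follows from the definition of the two classes and needs no assumed event rate. The primary endpoint is unaffected. The change is worth making because it costs little, but it buys visibility, not power.

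The two sections also need reconciling. One places the safety analysis at the 20th randomisation, the other at the end, and the article does not say whether these are two analyses or one. The outpatient-day condition removes participants who die in hospital. A reader might infer that it removes all in-hospital events. It does not: it restricts participants, and in-hospital events of those later discharged would still count.

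A reader might also infer that the trigger itself is an error. The documents do not support that. An early look has value when training starts 12 to 24 h after PCI, and 17 of 20 participants would have at least 7 days of follow-up. That only about 8 of 20 would have 30 days is a reason to update the table, not to move the look. Both counts rest on uniform accrual.

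**What to change.** - In Study Oversight and in Assessment and Reporting of Adverse Events, tabulate all adverse events by randomised arm regardless of attribution, with attribution as a secondary column. State that the display is descriptive.
- Base the safety analysis on all randomised participants, including in-hospital events, and remove the condition of at least one outpatient day.
- State in both sections whether there is an interim and a final safety analysis, and when each takes place.
- Keep the look at the 20th randomisation. Optionally, update the same table when that participant reaches day 30. Recruitment need not pause; about 11 more participants would be enrolled by then under uniform accrual.

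The cost is a different table layout and, if the update is used, one more tabulation by the existing three-person committee.

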### Study Population

The inclusion criteria are as follows: (1) age ≥ 18 years; patients with AMI undergoing primary PCI, admitted to the cardiac intensive care unit and at a high risk for pneumonia; and (2) be able to understand and agree with informed consent.

The exclusion criteria are: (1) a history of cerebrovascular accident; (2) have been treated with immunosuppressive medication for 30 days before the study; (3) have a neuromuscular disorder; (4) have cardiovascular instability (such as aortic dissection or unstable hemodynamics); (5) a history of coronary artery bypass grafting (CABG); (6) expected survival is < 6 months due to non-cardiogenic disease; (7) participated in other drugs or devices studies within 30 days; (8) confirmed ventricular aneurysm; and (9) other conditions not suitable for the study after the discussion among the researchers (e.g., poor compliance and unable to cooperate for the training).

After reviewing the results of previous studies and the clinical risk factors for pneumonia (1, 2, 7, 10), the following parameters will be used for pneumonia risk calculation: (1) age > 55 years; (2) history of diabetes mellitus, (3) present smoker; (4) chronic kidney disease [estimated glomerular filtration rate (eGFR) < 60 mL/min/1.73m^2^)]; and (5) forced expiratory volume in the first second of expiration (FEV_1_) <80% predicted and FEV_1_/forced vital capacity (FVC) <70% predicted. Having two or more of these parameters is regarded as being high risk for pneumonia.

### Randomization

A specific computer-generated, randomized number will be placed in a sealed envelope. Researchers will be blinded to the information in envelopes and will select consecutive envelopes to distribute to consecutive participants, thus randomly assigning them to either the IMT group (*n* = 30) or the control group (*n* = 30). See study flow Figure 1.

**Figure 1 F1:**
[figure not shown]
Study flow chart.

### Invention: IMT

For the IMT group, IMT will be performed for 15 min *per session*, twice a day, with an initial load of 30% of MIP using a threshold inspiratory muscle trainer (c-type, Shengchang medical equipment factory, Yuyao City, China). During the hospital period, the resistance will increase incrementally, based on the rate of perceived exertion scored on the Borg scale (11). If the rate of perceived exertion is <5, the resistance of the inspiratory threshold trainer will then be increase incrementally by 5%. To facilitate training for participants, the load for home-based IMT training will be set at the highest training load achieved while the patient was in hospital. All of the participants will be required to complete maneuvers in the seated position during training, wearing nose-clips. IMT will be performed every day from 12 to 24 h after primary PCI and the final session will be performed 30 days post-randomization. Participants in the control group will receive standard care after primary PCI according to the current clinical practice guidelines (12), which included risk stratification, continuous monitoring and specific nursing. And we also encourage an early ambulation, based on the complications, symptoms, and capacity.

### Baseline Characteristics and Medicine

Electrocardiogram will be performed before primary PCI, and repeated testing will also be required. Transthoracic echocardiography will be performed within 24 h after primary PCI, mainly for early identification of cardiac rupture or ventricular aneurysm. X-ray and/or pulmonary computed tomography will be performed to diagnose pneumonia, and repetitive testing should be considered if necessary. A loading dose of antiplatelet agents will be given before coronary angiography and all of the catheter techniques will be performed according to guidelines (13). During the intervention procedure, intra-aortic balloon pump or other invasive equipment will be used if necessary. For the in-hospital stay, medications, such as antiplatelet agents, angiotensin-converting enzyme inhibitors, and β-blockers, will be prescribed by the cardiologists as needed.

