### Follow-Up

Participants will be followed by two experienced researchers every week through phone interviews after discharge. Details of IMT will be documented, quality assessment will be performed, and any reported adverse events will be followed up, with assistance provided if necessary. All of the participants will be asked to return to the clinic for follow-up visits at 30 days post-randomization.

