##### Pneumonia

Pneumonia will be defined as the presence of a new or progressive radiographic infiltrate plus at least two of three clinical features (fever > 38°C, white blood cell count [WBC] > 10 × 10^9^/L or < 4 × 10^9^/L and purulent secretions), based on American Thoracic Society guidelines (15). Events of pneumonia will be followed and recorded by experienced doctors when participants are in hospital. After discharge, participants will be followed by experienced researchers and if a diagnosis of pneumonia is considered possible, guidance will be provided for the patients to complete necessary examinations, until 30 days post-randomization.

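### No masking of pneumonia assessment is described in an open comparison with discretionary imaging, and with about 1 to 4 expected cases a single call can move the odds ratio a long way

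*Protocol article*

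**What the plan says.** Only the protocol article is at hand.

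- **Comparison.** Controls receive usual care (Abstract; Invention: IMT). No sham device is described.
- **Blinding.** The only statement is under Randomization: "Researchers will be blinded to the information in envelopes". This is allocation concealment and does not cover outcome assessment.
- **Imaging** (Baseline Characteristics and Medicine): "X-ray and/or pulmonary computed tomography will be performed to diagnose pneumonia, and repetitive testing should be considered if necessary".
- **In hospital** (Pneumonia): "Events of pneumonia will be followed and recorded by experienced doctors when participants are in hospital".
- **After discharge** (Pneumonia): "if a diagnosis of pneumonia is considered possible, guidance will be provided for the patients to complete necessary examinations". The weekly telephone contacts are described under Follow-Up: "Details of IMT will be documented, quality assessment will be performed, and any reported adverse events will be followed up".
- **Case definition** (Pneumonia): "the presence of a new or progressive radiographic infiltrate plus at least two of three clinical features". The features are temperature, white cell count and purulent secretions.
- **Safety committee** (Study Oversight): "The cardiologists will be responsible for the review of the in-hospital course and follow-up adverse events of the participants". Events are then divided by whether they are associated with IMT.
- **Analysis** (Data Analysis): pneumonia is compared between arms by an odds ratio.

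**The concern.** Staff can see who trains. Several steps lie between a patient having pneumonia and being counted as a case: suspicion, choice of modality, repeat imaging, reading of the film, and the judgement on secretions. Each leaves room for expectation to act if the person taking it knows the arm. For the weekly callers this knowledge comes with the task, because they record training details in the same contacts in which they follow up adverse events.

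The fixed definition limits this but does not remove it. The Discussion concedes that fever and white cell count lose meaning in the inflammatory phase after infarction and may produce excess diagnoses. If those two numeric features are met because of the infarction itself, the reading of the infiltrate decides the case. Otherwise purulent secretions count as well. Both are judgements, and whether an image exists at all is discretionary.

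Pneumonia is a secondary endpoint, but the Discussion calls its prevention an important aim and says that the sample was enlarged with pneumonia especially in mind. A between-arm estimate will be reported, and with few cases it depends on one or two classifications.

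**Working it through.** **1. The plan's own figure.** Sample Size Calculation gives a difference of 15 cm H2O, SD 12, α = 0.05 (two-sided, from Data Analysis) and power 0.80.

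n per group = 2 × (1.96 + 0.84)² × 12² / 15² = 2 × 7.84 × 0.64 = 10.04, rounded up to 11.

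With 20% attrition: 11 / 0.8 = 13.75, rounded up to 14. Both stated figures reproduce. The primary endpoint thus needs 28 patients. The other 60 − 28 = 32 are enrolled for the secondary endpoints. No sample size, power or event count is stated for pneumonia.

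**2. Expected cases.** The Introduction gives 2–7% for acute myocardial infarction in general. No rate is given for the high-risk cohort. With 30 per arm and no treatment effect:

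- 2%: 30 × 0.02 = 0.6 per arm, 1.2 in total
- 7%: 30 × 0.07 = 2.1 per arm, 4.2 in total
- 10% (an assumption, to show a higher rate): 30 × 0.10 = 3 per arm, 6 in total

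**3. What one call does.** For a cases in the IMT arm and b in the control arm, OR = a(30 − b) / [b(30 − a)].

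| IMT v control | Calculation | OR | Fisher p |
|---|---|---|---|
| 1 v 1, 2 v 2, 3 v 3 | equal counts | 1.00 | 1.0 |
| 1 v 2 | 28 / 58 | 0.48 | 1.0 |
| 2 v 1 | 58 / 28 | 2.07 | 1.0 |
| 2 v 3 | 54 / 84 | 0.64 | 1.0 |
| 3 v 2 | 84 / 54 | 1.56 | 1.0 |
| 3 v 4 | 78 / 108 | 0.72 | 1.0 |
| 4 v 3 | 108 / 78 | 1.38 | 1.0 |

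- From 1 v 1, adding a case gives 2.07 or 0.48. Removing one gives 0 or an infinite value.
- From 2 v 2, removing a case gives 0.48 or 2.07. Adding one gives 1.56 or 0.64.
- From 3 v 3, removing a case gives 0.64 or 1.56. Adding one gives 1.38 or 0.72.

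So halving or doubling occurs when one arm moves between 1 and 2 cases. With more cases the effect of one call shrinks.

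**4. Significance.** With no case in one arm, p < 0.05 needs at least 6 in the other (0 v 5: p = 0.052; 0 v 6: p = 0.024). One altered call in the table above does not create a significant result. It changes the point estimate.

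**5. Who knows the arm.**

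| Role | What the article supports |
|---|---|
| Weekly telephone callers | Know the arm, since they record training details |
| In-hospital doctors recording pneumonia | Masking not stated either way |
| Readers of X-ray and CT | Not named; masking not stated |
| Two committee cardiologists | Masking not stated; the later division by IMT association in practice needs the arm |

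**The case against.** **A condensed article may omit who adjudicates a secondary endpoint.** This is a fair limit, and the full protocol may name a masked assessor. But the article does describe how pneumonia is found and recorded. It leaves the steps to discretion and gives the follow-up to people whose task reveals the arm. Followed as written, it exposes the estimate to ascertainment bias.

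**A reader might infer that everyone who suspects, images and classifies pneumonia is unmasked.** The article does not say so. Only the callers clearly know the arm. For the doctors, the image readers and the cardiologists it is silent.

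**A reader might also infer that trained patients are watched more closely, so that their cases are found more often.** Vital signs and adverse events are indeed recorded during in-hospital training sessions (Feasibility). However, all participants are admitted to the cardiac intensive care unit, usual care includes continuous monitoring, and the weekly calls and the 30-day visit are described for participants generally. Unequal detection is possible but not shown.

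**The arithmetic measures few events, not bias.** This stands. A correct masked call moves the odds ratio just as far as a biased one. The figures show how little error the estimate can absorb, and do not show that error will occur. The article already lists small sample size and possible over-diagnosis as limitations.

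**Masked review cannot recover cases never suspected or imaged.** This also stands, and the fix has to say so.

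**Conclusion.** The point holds as a gap in the described assessment of a secondary endpoint: an open comparison, discretionary imaging, arm-aware follow-up callers, and no masked step before a case is counted. At 2–7% and 30 per arm, about 1.2 to 4.2 cases are expected in total. One call then halves or doubles the odds ratio if an arm moves between 1 and 2 cases, and shifts it to between 0.64 and 1.56 from 3 v 3.

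This rests on three assumptions: the general infarction rate applies, the underlying rates are equal in the two arms, and all 30 per arm are analysed. A cohort selected for high risk may have more cases, and one call would then matter less.

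The documents do not support the stronger conclusions that the odds ratio will be biased, that a factor of two applies generally, or that a false significant finding would follow from one call. The primary comparison of maximal inspiratory pressure and its sample size are unaffected. This is a cheap improvement and not a defect that threatens the trial.

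**What to change.** 1. Leave clinical imaging as it is.
2. Have the two cardiologists who already review each in-hospital course and the follow-up events apply the protocol's pneumonia definition to every suspected case. They should work from an extract with the arm and all training details removed.
3. Lock that classification before events are classed as IMT-related or not, since that step in practice needs the arm.
4. Leave the arm off imaging requests.
5. Report per arm the number of suspected cases, chest X-rays and CTs. State that masked classification does not remove bias in who is suspected or imaged.

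**Cost.** Preparation time for extracts on a handful of suspected cases, and a short addition to the protocol. No new reader or procedure is needed. The cardiologists may be partly unmasked for a patient whose earlier safety event they have already reviewed. The classification should be in place before the first case is judged, because masking cannot be restored afterwards.
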